## Abstract

**Background:**

Ambulatory geriatric rehabilitation (AGR) is a community based outpatient intervention which aims to improve physical function, maintain independent living of geriatric patients, avoiding hospitalisation and institutionalisation. It should therefore reduce health care costs. The objective of our study is to evaluate the effectiveness of AGR for frail elderly patients insured by the statutory health insurance AOK Nordost compared to care as usual. Outcome variables are progression to higher nursing care levels, admission to nursing home, incident fractures, hospital admission, ambulatory care sensitive hospital admissions, days spent in hospital, and health care costs.

**Methods:**

This matched cohort study aims to estimate average treatment effects of AGR. For this purpose we will compare patients receiving AGR with matched patients receiving care as usual. Patients in the intervention group were treated between the years 2009 and 2013 from three centres in Mecklenburg-Vorpommern, Germany. Matching will be conducted using propensity score techniques. Claims data will be provided by the statutory health insurance AOK Nordost. The primary outcomes are the progression of nursing care levels, incident fractures, and admission to nursing home. Secondary outcomes are total and ambulatory care sensitive hospital admissions, and health care costs from the statutory health insurance perspective. Data will be analysed using appropriate regression models.

**Discussion:**

This study aims to quantify the effectiveness of AGR. Results will be important for providers of AGR, policy makers and stakeholders to make informed decisions on whether to continue, modify or extend AGR.

**Trial registration:**

German Clinical Trials Register (DRKS) S00008926, registered 29.07.2015

## Background

Many elderly will experience a reduction in physical function, leading to more falls and injuries. This leads to a loss of independence, hospitalisation, long-term nursing home care as well as premature death [1, 2]. In 2013, 2.63 million people in Germany were in need of nursing care. Roughly two third of them received ambulatory nursing care and one third received care in a nursing home. From the years 2011 to 2013, people receiving nursing care increased by 5% [3]. In 2014, 27% of the population aged 65–79 received either ambulatory or institutionalised nursing care [4]. Given the projected demographic changes in Germany, the population in the age group ≥65 years will increase from 21% (17.3 million) in the year 2015 to 27% (21.8 million) in the year 2030 [5]. Long term nursing care and institutionalisation in a nursing home can be associated with a significant reduction of quality of life, mainly due to loss of autonomy and social contacts [6]. The increased need of long term nursing care poses a major economic challenge [7]. Thus measures to prevent, minimise or delay long term nursing care for elderly are urgently needed.

Germany has mandatory nursing care insurance attached to statutory health insurance since 1995. Elderly with disabilities or dementia can apply for a nursing care level [*Pflegestufe*]. To identify elderly in need, a basic geriatric assessment performed in general practice was introduced in 2005 [8]. Although elderly are entitled to rehabilitative services as codified in the Book V (SGB V) and XI (SGB XI) of the German social code general practitioners have only limited access to specialised rehabilitative services for geriatric patients. While the number of hospitals providing geriatric services is increasing, the demand for ambulatory services is not met [9]. Elderly patients with a need for rehabilitation prefer to stay close to their home and relatives, maintaining their everyday life [10]. Consequently, ambulatory rehabilitation is preferred. Rehabilitative services were and are still mainly available after hospitalisation e.g. for stroke or fracture after a fall.

Preventive ambulatory geriatric rehabilitation (AGR [*Ambulante Geriatrische Komplexbehandlung*]) was introduced in 2008 within the legal frame (§ 140 Book V of the social code) of selective contracts for integrated care. Therefore it is only available as a model intervention in some areas for holders of specific statutory health insurances (e.g. AOK Nordost). AGR is not part of regular health care.

It is intended as a community based outpatient intervention to improve patient’s physical function, increase patient’s safety and quality of life as well as to prevent falls and injuries, to avoid and delay hospitalisation, the progression of nursing care level and admission to nursing home.

A systematic review of controlled trials of ambulatory and hospital interventions to improve physical function and maintain independent living in elderly people concluded that they were effective to achieve the goal [1]. This review comprised only one German trial which included geriatric patient post hospital discharge [11]. However, AGR is primarily intended to prevent hospitalisation and not as a post-discharge rehabilitation. The effectiveness of German AGR programs has not been evaluated rigorously yet. Previous studies have relied on uncontrolled study designs [12].

### Objectives and hypotheses

The aim of our study is to evaluate the effectiveness of AGR regarding patient’s progression to higher nursing care levels, incident fractures, admission to nursing home, hospital admissions as well as health care costs. For this purpose we compare patients receiving AGR with patients receiving care as usual. We will estimate average treatment effects based on a cohort design using propensity score techniques to match cases and controls. The follow-up period will be up to 2 years.

*Our primary hypotheses are*:AGR reduces and delays progression to higher nursing care levels.AGR reduces and delays nursing home admissions.AGR reduces the risk of incident fractures.

*Our secondary hypotheses are*:AGR decreases and delays hospital admissions and reduces the days spent in hospital during follow-up time.AGR decreases and delays ambulatory care sensitive hospital admissions.AGR decreases total health care costs from the statutory health insurance perspective.

On an exploratory basis we will investigate the effect on drug prescriptions.

## Methods

### Study design

The conduct of a randomised controlled trial to assess the effectiveness of AGR is currently limited due to logistic and ethical reasons. Therefore we will conduct a matched cohort study using claims data. Anonymised data will be provided by the statutory health insurance AOK Nordost which comprises basic demographic data, data on nursing care level, admission to a nursing home, billing data for ambulatory services (EBM position numbers) and for hospital services (DRG-codes/OPS-codes), as well as diagnoses (ICD-10 codes), and all health care costs, including costs for hospitalisation, remedies and aids, ambulatory costs and costs for medication. To balance potential confounders, we will apply a propensity score matching. Controls will be matched patients insured by the AOK Nordost.

The observation period comprises 4 billing periods (each 3 months, corresponding to 1 year) prior to the intervention, the intervention (index) billing period, and up to 8 billing periods post intervention, resulting in a total observation period of up to 13 billing periods. The billing period covering the most days of the intervention will be considered as the index billing period. Participants in the intervention group received a 4 weeks AGR in between the years 2009 and 2013.

### Description of the AGR intervention and the setting

AGR is a multimodal intervention consisting of physiotherapy, ergotherapy, speech therapy, occupational therapy, social support by qualified social workers, psychological counselling and counselling regarding aids and care. Patients who are deemed suitable for AGR by their general practitioners can be referred to special rehabilitation centre for a geriatric assessment. If they fulfil eligibility criteria for AGR and agree to participate they receive the intervention. The intervention is tailored to the patients’ needs and delivered in individual and group sessions. Patients are commonly treated for a total of 20 days with two to three 30 min therapy units per day. Included are meals and a pick up and return service for the elderly every day. During the intervention period AGR was available in three locations in Mecklenburg-Vorpommern (Trassenheide, Ueckermünde, Waren) (Fig. 1).

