### Eligibility criteria for AGR

Due to selective contracts only patients insured by the AOK Nordost are entitled to receive AGR. The geriatric assessment comprises the activity of daily living scale (Barthel-Index), instrumental activity of daily living, Timed “Up & Go”, Chair-Rising-Test, Tandem Stance, Berg-Balance-Scale, and handgrip strength. Eligibility criteria are:Aged 70 and olderat least two geriatric multimorbidity listed in Table 1
impairment or handicap with functional deficitsat least one of the health conditions listed in Table 2

**Table 1 Tab1:** Geriatric multimorbidity

Criteria	ICD-10 codes
Immobility	M96.8, M62.3, M62.5
cognitive impairment	G30, F00 – F07
incontinence	R32, N39, R15
decubitus ulcer	L89, L97, I83, L98
Malnutrition	R64, E41, E43, E44
Disturbances in fluid and electrolyte balance	E86, E87, R60
Depression and Anxiety	F30 – F33, F40, F41
chronic pain	R52
paraesthesia	R20, G50 – G59, G60 – G64
frailty	R54
severe visual or hearing impairment	H25, H28, H52-H54, H90, H91

**Table 2 Tab2:** Eligibility criteria for participation in AGR

Eligibility criteria	ICD-10 codes
Stroke and other cerebrovascular disorders	I60-I69
Status post fracture	S72.-
Arterial obstructive disease with amputation or other surgery	I70.-
Cox and osteoarthritis with Implantation of an endoprosthesis	M16.-, M17.-
Heart failure	I50.-
Exacerbated chronic obstructive pulmonary disease	J44.0, J44.1
Pneumonia and other respiratory tract infections	J10-J22
Other fractures and injuries	S00-T98
Other arthropathies	M00-M25
Spondylopathies and Discopathies, possibly with laminectomy	M45-M51
Coronary heart disease and other heart diseases with cardiac surgery	I05-I09; I20-I25
Delirium and other organic brain psychosis	F00-F05
Osteoporosis	M80-M81
Secondary Parkinsonsyndrom	G20.9
Symptoms, effecting the nervous system and musculoskeletal system	R29.5, R29.6, R29.8

Patients are not eligible for AGR if the assessment indicates a need for hospital admission, if they are not able to participate due to a poor health status or if they are unable to provide informed consent.

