Pneumonia and other lung inflammations	x ^a^	x
*Cardio*-*vascular system*		
Heart failure		
Chronic obstructive pulmonary disease (COPD)		x
Arterial obstructive disease with amputation or other surgery	x ^a^	x
Coronary heart diseases with surgery		x
Stroke and other cerebrovascular diseases		x
*Neuro*-*psychiatric*		
Delirium and other organic brain psychosis		x
Secondary Parkinsonsyndrom	x ^a^	x
Symptoms, effecting the nervous system and musculoskeletal system		x
Charlson Comorbidity Index		
Any Malignancy	x	x
Cerebrovascular disease		x
Chronic pulmonary disease		x
Congestive heart failure		x
Metastatic solid tumor	x	
Dementia	x	x
Hemiplegia or paraplegia		x
Mild liver disease		x
Myocardial infarction		x
Renal disease		x
Peripheral vascular disease		x
Geriatric Multimorbidity		
Cognitive deficit		x
Chronic pain		x
Depression, Anxiety		x
Incontinence		x
Severe visual/hearing impairment		x
Paraesthesia		x
Immobility	x	x
Chemotherapy	x	x

^a^At least one diagnosis from each main diagnosis group will be used to match controls. Diagnoses are allowed to differ between cases and controls within the main diagnoses group

Subsequently, propensity scores will be calculated using a logistic regression model using coded morbidity and costs under the scenarios a.) and b.), based on all variables listed in Table 6, taking statistical interactions and nonlinear associations into account. Up to four controls may be assigned to one case without repetition.

Appropriate regression models (e.g. time-event models, mixed models, two-part models) will be applied to study effects on our primary and secondary outcomes. Because treatment might also affect censoring due to mortality, competing risks models (using the Fine-Gray approach) will be applied [17]. Patients dying during the follow-up period will not be excluded from the analyses.

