## Discussion

AGR is currently only available in few areas for elderly people from selected statutory health insurances which opted to offer AGR to their beneficiaries. Evaluation of this intervention was previously limited to uncontrolled study designs [12]. To the best of our knowledge, this will be the first study to evaluate AGR using a quasi-experimental design. This study may provide an estimation of the effectiveness of AGR on progression to higher nursing care levels and hospitalisation and other endpoints of clinical relevance. Our results will be important for providers of AGR, policy makers and stakeholders to make informed decisions on whether to continue, modify or even expand AGR to other areas in Germany. Additionally, our results might help to optimise AGR by identifying subgroups of patients who are more likely to benefit from AGR.

A limitation will be the restriction to claims data. Clinical measurements from instruments used for the geriatric assessment are not available for the control group. This might impair the quality of the matching as potential imbalance between clinical data and individual motivation to participate in AGR cannot be ruled out even if a high balance on claims data is achieved. Therefore, residual confounding may still be an issue after our matching. Final decisions on the applied methods need to account for the precise properties of the data.

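### Table 6 captures take-up of care only through cost totals, so confounding by health-seeking is reduced less than the supplied billing codes would allow

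*Protocol article*

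**What the plan says.** All references are to the protocol article.

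**Selection into treatment.** The section describing the AGR intervention and its setting gives three steps: GP judgement, assessment, consent. "Patients who are deemed suitable for AGR by their general practitioners can be referred to special rehabilitation centre for a geriatric assessment". Then: "If they fulfil eligibility criteria for AGR and agree to participate they receive the intervention". Under Eligibility criteria for AGR, patients are also ruled out "if they are not able to participate due to a poor health status or if they are unable to provide informed consent". The programme is a substantial commitment: four weeks, commonly 20 treatment days.

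**Covariates.** Matching and statistical analyses says propensity variables are chosen for their expected value in predicting both AGR participation and the outcomes. The score is then "based on all variables listed in Table 6". That table holds demographics, area of residence, insured days, nursing care level, hospital use, diagnoses and comorbidity. It also holds costs for hospital, ambulatory care, remedies, aids and drugs, and in total.

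**Data supplied.** Study design lists, among the claims data, "billing data for ambulatory services (EBM position numbers"). Outcome measures and data collection adds that variables are provided for every billing period.

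**Acknowledged limitation.** The Discussion says that imbalance in clinical data and "individual motivation to participate in AGR cannot be ruled out even if a high balance on claims data is achieved", and that residual confounding may remain.

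**The concern.** The treated patients are people whom a GP referred and who then said yes. Willingness to accept offered care plausibly predicts later outcomes whatever the programme does. It is therefore a candidate confounder by the protocol's own selection rule, and the Discussion names it.

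The cost totals in Table 6 are a weak handle on it. A high ambulatory or drug cost can mean a sick patient, a patient who readily uses services, or both. Two people with equal cost and equal coded morbidity can still differ in how readily they take up care. The position numbers might separate these more finely, but Table 6 contains no variable built from them for this purpose.

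The results are meant to inform whether AGR is continued, changed or extended. A modest difference in a primary outcome would be hard to interpret if a named confounder had been adjusted for only through costs.

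**Working it through.** **1. The plan's own figure.** About 700 AGR patients with up to four controls each gives 700 × 4 = 2800, which matches the stated number of controls. The article gives no event rate, effect size or significance level, so there is no power figure to reproduce.

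**2. What Table 6 contains.**

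| Aspect | In Table 6 | Reflects |
|---|---|---|
| Ambulatory, remedy, aid and drug costs | Yes, as totals | Need and uptake mixed |
| Hospital admission, days, costs | Yes | Mainly illness |
| Diagnoses, comorbidity, care level | Yes | Morbidity and need |
| Contact pattern or preventive-service use | No | Uptake more directly |

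The planned comparison of scenarios a and b does not fill this gap. It concerns the timing of events around the index period.

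**3. How large could the bias be?** The inputs here are assumptions, because the documents give none. Take one binary trait with prevalence p1 in AGR patients and p0 in controls after matching, and risk ratio RR for the outcome. If AGR has no effect, the observed ratio is

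B = [1 + p1(RR − 1)] / [1 + p0(RR − 1)].

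With p0 = 0.5:

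- Smallest case, p1 = 0.6, RR = 0.9: 0.94 / 0.95 = 0.989.
- Middle case, p1 = 0.7, RR = 0.7: 0.79 / 0.85 = 0.929.
- Largest case, p1 = 0.9, RR = 0.6: 0.64 / 0.80 = 0.800.

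The range is about 0.80 to 0.99, a spurious reduction of roughly 1% to 20%.

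**4. The sign is an input, not a result.** If the same trait raised the recorded event rate, say RR = 1/0.8 = 1.25 with 70% against 50%, then B = 1.175 / 1.125 = 1.04, and a null programme would look slightly harmful.

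**5. What a bias of this order would do.** Assume a simple comparison of two proportions, 700 against 2800, two-sided 5% level, ignoring the matching. The chance of a nominally significant benefit when AGR does nothing is then:

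| Assumed control risk | Spurious ratio 0.95 | Spurious ratio 0.90 |
|---|---|---|
| 10% | 6% | 12% |
| 20% | 8% | 22% |
| 30% | 12% | 34% |

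Without bias it is about 2.5% in that direction.

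**6. The optional bias analysis.** For an observed ratio below 1, put r = 1/ratio; the E-value is r + √[r(r − 1)]. Ratios of 0.9, 0.8 and 0.7 give 1.46, 1.81 and 2.21. These are the strengths of association, on the risk-ratio scale, that an unmeasured confounder would need with both treatment and outcome to explain the estimate away.

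**The case against.** **Already disclosed, and methods left open.** The Discussion states the limitation and says that final choices of method depend on the properties of the data. An analysis plan that is not shown may include a bias analysis. This stands as far as it goes: nothing is hidden, and the absence of a bias analysis from a journal article is not a fault. The covariate list, however, is set out in the article itself, and disclosing a confounder does not adjust for it.

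**A reader might infer that Table 6 has no proxy at all for take-up of care.** The documents do not support that. Ambulatory, remedy, aid and drug costs record services actually used, and drug costs also enter the pre-matching. They are crude proxies, not absent ones.

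**A reader might infer that the remaining bias favours AGR on all three primary outcomes.** This is not shown. AGR patients had to have functional deficits, and the assessment scores are unavailable for controls, so unmeasured need could count against AGR. Nursing care levels must be applied for (Background), so people who readily seek services might reach a higher level sooner. Exclusion of those too ill or unable to consent pushes the other way.

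**A reader might infer that controls were never offered AGR, or that treated patients were selected for completing it.** The article says neither. The treated group is all participants, so only selection on uptake is supported.

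**Feasibility.** The article does not say which preventive services the position numbers identify. A count of periods with GP contact also mixes need with uptake. Both points stand and limit what the fix can achieve.

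**Conclusion.** The point holds in a limited form. Selection by referral and consent is stated, motivation is named as a possible residual imbalance, and Table 6 reflects take-up of care only through cost totals while finer billing data are supplied. Confounding by health-seeking is thus likely to be reduced less than the data allow.

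This component taken alone would tend to favour AGR on some outcomes. The net direction of residual confounding is unknown. The 0.80-0.99 range and the false-positive chances are illustrations: they rest wholly on assumed prevalences, risk ratios and control risks, on a trait assumed to be protective, and on the imbalance persisting after matching on costs. They show that the issue could matter, not that it does. The change is worth making because it is cheap and addresses a confounder that the protocol itself identifies.

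**What to change.** Add to the propensity score in Table 6, measured over the four billing periods before the index period:

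- the number of periods with GP contact;
- use of any preventive service that can be identified from the ambulatory position numbers.

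Use the same pre-index window under scenarios a and b, since contact during the index period may be part of the referral to AGR. Report balance on both covariates after matching, alongside the other Table 6 variables.

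Optionally, report a simple bias analysis for each primary outcome, such as the E-value of the estimate and of its confidence limit. This removes no bias; it only helps a reader judge how robust the result is.

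**Cost.** A few derived variables from data already requested, a few more terms in the propensity model, and, if chosen, one extra line of output per primary outcome. Availability in the codes has to be checked first, and the proxies remain imperfect, so the limitation in the Discussion should stay.

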**Fig. 1 Fig1:**
[figure not shown]
Map of Mecklenburg-Vorpommern with the three locations which provided AGR

### Eligibility criteria for AGR

Due to selective contracts only patients insured by the AOK Nordost are entitled to receive AGR. The geriatric assessment comprises the activity of daily living scale (Barthel-Index), instrumental activity of daily living, Timed “Up & Go”, Chair-Rising-Test, Tandem Stance, Berg-Balance-Scale, and handgrip strength. Eligibility criteria are:Aged 70 and olderat least two geriatric multimorbidity listed in Table 1
impairment or handicap with functional deficitsat least one of the health conditions listed in Table 2

**Table 1 Tab1:** Geriatric multimorbidity

Criteria	ICD-10 codes
Immobility	M96.8, M62.3, M62.5
cognitive impairment	G30, F00 – F07
incontinence	R32, N39, R15
decubitus ulcer	L89, L97, I83, L98
Malnutrition	R64, E41, E43, E44
Disturbances in fluid and electrolyte balance	E86, E87, R60
Depression and Anxiety	F30 – F33, F40, F41
chronic pain	R52
paraesthesia	R20, G50 – G59, G60 – G64
frailty	R54
severe visual or hearing impairment	H25, H28, H52-H54, H90, H91

**Table 2 Tab2:** Eligibility criteria for participation in AGR

Eligibility criteria	ICD-10 codes
Stroke and other cerebrovascular disorders	I60-I69
Status post fracture	S72.-
Arterial obstructive disease with amputation or other surgery	I70.-
Cox and osteoarthritis with Implantation of an endoprosthesis	M16.-, M17.-
Heart failure	I50.-
Exacerbated chronic obstructive pulmonary disease	J44.0, J44.1
Pneumonia and other respiratory tract infections	J10-J22
Other fractures and injuries	S00-T98
Other arthropathies	M00-M25
Spondylopathies and Discopathies, possibly with laminectomy	M45-M51
Coronary heart disease and other heart diseases with cardiac surgery	I05-I09; I20-I25
Delirium and other organic brain psychosis	F00-F05
Osteoporosis	M80-M81
Secondary Parkinsonsyndrom	G20.9
Symptoms, effecting the nervous system and musculoskeletal system	R29.5, R29.6, R29.8

Patients are not eligible for AGR if the assessment indicates a need for hospital admission, if they are not able to participate due to a poor health status or if they are unable to provide informed consent.

